## Abstract

Promising initial studies on vitamin D (VD) supplementation as an adjunct treatment for major depressive disorder (MDD) require rigorously designed randomized controlled trials (RCTs). We aim to investigate the effects of augmenting standard MDD treatment with VD supplementation and examine factors influencing the treatment outcome. This article describes the study design, measures, and baseline characteristics. This multicenter RCT compares the efficacy of a six‐month VD intervention at 100 micrograms/day versus 10 micrograms/day (μg/day) (4000 IU (international units)/day vs. 400 IU/day) added to a standard treatment in outpatients aged 20–61 years with MDD. The primary outcome is change in the Montgomery–Åsberg Depression Rating Scale (MADRS) score. Secondary outcomes are other indicators of mental health and functionality (BDI, SOC, 15‐D, PSS10, LS‐4, LOT‐R, YSQ‐S2‐extended, CORE‐OM, TAS‐20, BRCS, TADS, SCL‐90, DIAD, GAF), and circulating biomarkers. Intervention assessments are conducted at baseline, 3, and 6 months, and follow‐ups at 18 months and 6 years post‐baseline. The baseline sample had 319 subjects (74% women; median age 31 (inter‐quartile range (IQR) 15), mean MADRS score 21.38 (SD 6.04)), with 281 assigned to the RCT. At present, the study continues as a follow‐up study. DepFuD project will provide extensive information regarding the potential benefits of VD and enables to identify various biopsychosocial depression‐associated risk factors.

## INTRODUCTION

1

### Background and rationale

1.1

Major depressive disorder (MDD) is a significant mental disorder affecting an estimated 6% of adults annually with a lifetime risk of 15%–18% (Malhi & Mann, 2018). Depression is more common in women than men and more common in older than younger adults (World Health Organization, 2023). Compared to matched controls, somatic comorbidity and healthcare utilization are accentuated in people with MDD diagnosis (Steffen et al., 2020). MDD impairs psychosocial functioning, quality of life (Yang et al., 2022), and the prognosis of comorbid chronic diseases (Saint Onge et al., 2014).

Despite available treatments, many patients with MDD remain untreated due to social stigma and lack of trained healthcare providers, especially in low‐ and middle‐income countries (World Health Organization, 2023). In addition, resource scarcity may result in a greater reliance on pharmacological over psychological treatments (Cipriani et al., 2018). Antidepressants are an effective treatment for correctly diagnosed MDD (Cipriani et al., 2018), but many patients require multiple trials to achieve sufficient therapeutic response, and relapses are common (Rush et al., 2006). The heterogeneity of MDD coupled with an incomplete understanding of its pathophysiology hinders the development of more effective treatments (Malhi & Mann, 2018). Thus, research on novel treatment interventions and predictors of good treatment response is warranted.

The etiology of MDD is considered to be a combination of environmental, psychological, genetic, and biological factors (Lopresti et al., 2013). Depressive symptoms are linked to dysregulated inflammatory pathways, stress‐induced abnormal lipid and glucose metabolism (Berk et al., 2013), and a complex bidirectional relationship between endogenous inflammation and depression is suggested (Giollabhui et al., 2021). MDD is associated with compromised neurogenesis and neuronal plasticity in the brain and with hypothalamic–pituitary–adrenal (HPA) axis dysfunction (Willner et al., 2013). Dysregulated physiological pathways are influenced by stress, life events, and lifestyle factors, such as diet, physical activity, and sleep. In turn, the onset, progression, and treatment of depression can be shaped by these lifestyle factors (Lopresti et al., 2013).

Emerging evidence suggests that diet quality and nutritional components, such as vitamin D (VD), may impact the risk and progression of depressive disorders (Marx et al., 2021; Opie et al., 2017). In the central nervous system (CNS), VD is proposed to influence brain plasticity and neurotransmitter activity (Rejnmark et al., 2017), and antagonize the chronic stress effects on hippocampal neuronal differentiation and glucocorticoid receptor function (Cui & Eyles, 2022). Furthermore, human immune responses are promoted by 1,25‐dihydroxyvitamin D3 (1,25(OH)2D3) and affected by the bioavailability of circulating 25‐hydroxyvitamin D3 [25(OH)D] (Adams & Hewison, 2012).

Low 25(OH)D levels have been linked to depression in cross‐sectional studies (Anglin et al., 2013). For example, the Canadian Network for Mood and Anxiety Treatments (CANMAT) 2023 Update on Guidelines for the Management of Adults with MDD suggests patient‐specific determination of vitamin D levels in the differential diagnosis if deficiency is suspected (Lam et al., 2024). However, the current CANMAT guidelines do not recommend vitamin D supplementation as an adjunct treatment for MDD (Lam et al., 2024). Recent meta‐analyses of randomized controlled trials (RCTs) conducted in various healthy and clinical populations suggest that VD supplementation may improve depressive symptoms compared to placebo (Cheng et al., 2020; Mikola et al., 2022) and potentially reduce incidence of depression (Xie et al., 2022). These findings, due to high heterogeneity and potential publication bias, require further validation from well‐documented, long‐term, high‐quality RCTs with a follow‐up. This article presents the study design and baseline characteristics for the trial: “A follow‐up study with a double‐blinded, randomized controlled vitamin D supplementation trial in patients with major depressive episode (DepFuD)” [ClinicalTrials.gov: NCT02521012].

### Objectives

1.2

The primary aim of the DepFuD clinical RCT is to compare the effect of a six‐month (“higher‐dose”) 100 μg (4000 IU (international units)) of VD (cholecalciferol)/day supplementation vs. (“lower‐dose”) 10 μg/day (400 IU) supplementation on depression treatment response. Secondary aims of the RCT include exploring the effect of VD supplementation on depression‐related inflammatory markers and long‐term recovery from depression. The main RCT hypothesis is that higher‐dose VD recipients will experience greater symptom reduction than lower‐dose VD supplementation recipients over 6 months. The secondary hypothesis is that depression‐related inflammatory markers differ between the RCT groups at the end of the supplementation. In addition, higher‐dose supplementation recipients are hypothesized to have better long‐term recovery from depression compared to lower‐dose supplementation recipients. The DepFuD follow‐up study also aims to identify biopsychosocial profiles predicting depression treatment response, despite VD intervention. Overall, the DepFuD project hypothesizes to be able to identify new group‐level biopsychosocial profiles predicting an individual's (a) positive treatment response in depression, (b) work ability, (c) overall mental health (including subjective wellbeing), and (d) personal and external resources.

### Trial design

1.3

DepFuD starts with a 6‐month clinical trial using a double‐blinded, parallel‐group, randomized controlled superiority design among psychiatric adult outpatients with a 1:1 allocation ratio. The follow‐up will continue up to 6 years after the trial baseline. DepFuD employs a multidisciplinary approach, integrating psychiatry, epidemiology, public health science, physiology, and biomedicine.

### Trial registration

1.4

The trial is registered in ClinicalTrials.gov (Identifier: NCT02521012) on August 13, 2015. All items from the World Health Organization Trial Registration Data Set can be found in the protocol and in the Table S1.

### Protocol version

1.5

Issue date: May 2024. This is the first open access version of the study protocol, edited according to the Standard Protocol Items: Recommendations for Interventional Trials (SPIRIT) guidelines (Chan et al., 2013). See Section 3.2 for protocol amendment details.

### Roles and responsibilities

1.6

The DepFuD project, coordinated by Kuopio University Hospital (KUH), Department of Psychiatry (Wellbeing Services County of North Savo), is led by the core group including AR, [name], KH, [name], [name], VL, TT, and the current corresponding investigator MP. The core group meets to make decisions regarding the research direction when needed. The project investigators are handling all aspects of the trial management without other formal groups involved in trial oversight, such as a steering committee, endpoint adjudication committee, or data management team. Formal committees were not deemed necessary due to the standard format study design and Finnish ethics regulations. See Section 2.14.1 Data monitoring for the rationalization of the lack of data monitoring committee. There are no sponsors.

## METHODS

2

### Study setting

2.1

### Eligibility criteria

2.2

See Table 1 for inclusion and exclusion criteria. The majority of depressed patients in the participating units were assumed to meet the inclusion criteria for the follow‐up study and the VD intervention. Subjects who did not meet the inclusion criteria for the intervention were, upon consent, included directly in the follow‐up study only.

**TABLE 1 fsn34417-tbl-0001:** Inclusion and exclusion criteria for the DepFuD study.

Follow‐up study	
Inclusion criteria	Exclusion criteria
Age: 18–65 years Sex: all Patient referred to the recruitment sites for treatment of depression Mild, moderate, or severe depression, or Mild, moderate, or severe depressive episode of recurrent depression	Psychotic depression, psychotic disorder, or bipolar disorder The person's state of health does not allow participation in the study (e.g., significant impairment of vision, hearing, or motor function) Severe substance addiction and its complications in the brain and central nervous system
*Randomized vitamin D intervention trial*	
*Vitamin D intervention trial will include all subjects eligible for the follow‐up study (same inclusion and exclusion criteria apply), with the following additional exclusion criteria:*	
Disease affecting vitamin D metabolism (sarcoidosis, hypoparathyroidism and hyperparathyroidism, hypercalcemia, kidney stones, kidney failure, or other disease affecting kidney function) Pregnancy or breastfeeding Current use of a vitamin D supplement (more than 10 μg 400 IU per day as ≤10 μg/day may be used regularly) Current use of a calcium supplement (more than 1200 mg/day)	

### Outcomes

2.3

#### Outcomes for the VD intervention

2.3.1

##### Primary

Between‐group differential change from baseline to 6 months in depressive symptoms as measured by the Montgomery–Åsberg Depression Rating Scale (MADRS) (range: 0–60). The changes in mean MADRS scores are compared between the subjects randomized to the higher‐dose VD supplementation group (100 μg/4000 IU per day) and the lower‐dose supplementation group (10 μg/400 IU per day).

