##### Secondary

Between‐group difference in the proportion of subjects experiencing response to depression treatment (defined as MADRS score decreased by ≥50%) from baseline to 6 months.

Between‐group difference in the proportion of subjects experiencing recovery from depression (MADRS score decreases to ≤10) (Zimmerman et al., 2004).

Between‐group difference in the changes in other scales and measures, such as Beck Depression Inventory (BDI) and the Symptom Checklist‐90 (SCL‐90), and changes in blood markers, including inflammatory biomarkers, between baseline and 6 months. See Figure 1 for the complete list of secondary outcomes and the time points for each outcome measure. The mean/median values are compared between the higher‐dose supplementation group and the lower‐dose supplementation group at baseline and at 6 months.

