### Sample size

2.5

The target sample size was derived from the VD intervention power calculation and was based on between‐group change in the MADRS score. The primary sample size calculation for DepFuD project was made in 2015 based on a small effect size of 0.15, by which the effect of the VD supplement was estimated to be at a clinically significant level, considering its benefit–risk ratio. In a two‐tailed test, with randomization ratio 1:1, alpha = 0.05, and power = 0.95, a total of 1211 individuals per intervention group should have been recruited to the study (a total of 2422 subjects). With accounting for attrition of 25%, a total of *n* = 3028 subjects would have been needed.

The target sample size was adjusted in 2019. According to previous literature, in adult patients with depression, an estimated minimal clinically important change in MADRS score during treatment was 1.6–1.9 points (Duru & Fantino, 2008). For DepFuD, a minimum of 4‐point improvement in MADRS score was considered as clinically important. With alpha = 0.05, power = 0.90, a between‐group difference of 4 units for MADRS mean, and a MADRS standard deviation (SD) = 12, a total of 382 subjects (191 per group) are required. Calculation was performed with PASS (Power Analysis and Sample Size) Software (NCSS, LLC., Kaysville, Utah) by an experienced statistician. Considering an estimated attrition of 25%, the study aimed to recruit a total of *n* = 478 subjects. The between‐group difference in MADRS mean values, which guided the determination of target sample size, is analyzed as the primary outcome, while response to treatment (defined as usual by arbitrary ≥50% MADRS score decrease from baseline) serves as a secondary outcome.

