### Statistical methods

2.13

Statistical analyses will be conducted with current versions of appropriate mainline statistical software: IBM SPSS Statistics for Windows (IBM Corp., Armonk, NY), R with suitable packages (R Foundation for Statistical Computing, Vienna, Austria), Stata Statistical Software (StataCorp, TX), or SAS software suite (SAS Institute Inc., NC). Continuous baseline and longitudinal data will be expressed as means with SDs or as medians with inter‐quartile ranges (IQRs)/ranges, whereas categorical variables will be expressed as proportions. Confidence intervals (95% CIs) will be calculated for risk ratios, for risk differences for categorical variables, and for mean differences for continuous variables. Baseline data will be analyzed cross‐sectionally for factors correlated with symptoms of depression. In cross‐sectional and longitudinal analyses e.g. analysis of variance (ANOVA), logistic or linear regression analysis, mixed models, and, if necessary, Cox regression analysis based on registry data will be utilized.

For the primary outcome, an intention‐to‐treat analysis will be performed for all randomized subjects who attended to all study visits during the intervention and completed study questionnaire without missing primary outcome data. RCT participants, who reported using over 10 μg (400 IU) of VD supplement outside the study almost daily at baseline or at 6 months despite prohibition, will be excluded from intervention analyses. Additional comparative analyses can be conducted with and without these participants. Subgroup analyses for the intervention data will be based on factors like baseline VD status, age, sex, and body mass index (BMI). If multiple effect estimates are generated for a specific outcome measurement, all estimates will be reported. Follow‐up analyses will consider background characteristics and secondary outcomes. The randomness and impact of missing data will be evaluated for primary and secondary outcome analyses, and imputation methods and sensitivity analyses may be used for specific subgroup analyses. KUH and UEF statisticians will be consulted for more advanced statistical models.

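### No model with baseline MADRS as a covariate is committed to for the primary comparison, and the stated contrasts (change, or group values by visit) are no more precise than an adjusted one

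*Protocol article*

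**What the plan says.** - **Primary outcome (Section 2.3.1, Primary).** The contrast is between-arm change in MADRS from baseline to 6 months: "The changes in mean MADRS scores are compared between the subjects randomized to the" higher-dose and lower-dose groups. No covariate is mentioned.
- **Secondary outcomes (Section 2.3.1, Secondary).** Other scales and blood markers are first defined as between-arm differences in change. The paragraph then adds a second description: "The mean/median values are compared between the" higher-dose group and the lower-dose "supplementation group at baseline and at 6 months".
- **Sample size (Section 2.5).** The section opens by basing the calculation on change in MADRS and closes by saying that the between-group "difference in MADRS mean values, which guided the determination of target sample size, is analyzed as the primary outcome". The planning SD of 12 is not tied to either the score or the change.
- **Statistical methods (Section 2.13).** The models are given as examples, among them "analysis of variance (ANOVA), logistic or linear regression analysis, mixed models". None is assigned to the primary outcome, and no baseline covariate is named.
- **Baseline data (Table 3).** MADRS has mean 21.38 and SD 6.04, with no missing values among 319 subjects.

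**The concern.** Where an outcome is measured before and after randomisation, a comparison of raw change subtracts the whole baseline value, and a comparison of 6-month values subtracts none of it. A model with baseline as covariate estimates the right amount from the data. Raw change therefore usually over-corrects for a chance baseline difference, because of regression to the mean, and a 6-month comparison under-corrects.

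This matters more than usual here because recruitment fell short: 281 were randomised against a target of 478 (281/478 = 59%). Section 2.13 then narrows the primary analysis to those with complete visits and primary outcome data, and removes users of off-protocol vitamin D. Baseline MADRS is already in hand for everyone, so leaving it out of the model would give up precision for nothing. Section 2.13 also foresees several estimates for one outcome, all to be reported. That is transparent, but it does not say which estimate is primary.

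**Working it through.** **1. The plan's own figure.** Inputs from Section 2.5: difference 4, SD 12, alpha 0.05, power 0.90. Two-sided testing is assumed, as in the 2015 calculation.

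n per group = 2 × (12/4)² × (1.960 + 1.282)² = 189.1, so 190 by the normal approximation. With the t distribution, power is 0.8999 at 190 and 0.9013 at 191 per group. The stated 191 per group (382) is therefore reproduced as an unadjusted two-sample t-test. The design calculation uses no baseline covariate.

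**2. Precision of change against ANCOVA.** Inputs: baseline SD s0 = 6.04 (Table 3, all 319 subjects). The 6-month SD s1 and the baseline-to-6-month correlation r are not in the document and are assumed.

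- Var(change) = s0² + s1² − 2·r·s0·s1
- Var(ANCOVA) = s1²·(1 − r²)

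| s1 | r | Var(change) | Var(ANCOVA) | Ratio |
|---|---|---|---|---|
| 6 | 0.2 | 57.99 | 34.56 | 0.60 |
| 6 | 0.5 | 36.24 | 27.00 | 0.75 |
| 8 | 0.3 | 71.49 | 58.24 | 0.81 |
| 8 | 0.4 | 61.83 | 53.76 | 0.87 |
| 8 | 0.5 | 52.16 | 48.00 | 0.92 |
| 12 | 0.3 | 136.99 | 131.04 | 0.96 |
| 12 | 0.5 | 108.00 | 108.00 | 1.00 |

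At s1 = 8 the ratios correspond to 8% to 19% fewer patients for equal precision. Against 6-month values alone the ratio is 1 − r², which is 0.91, 0.84 and 0.75 at r = 0.3, 0.4 and 0.5, whatever s1 is.

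**3. Chance baseline imbalance.** Inputs: 142 and 139 randomised (Section 5.1).

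- SE of the baseline difference = 6.04 × √(1/142 + 1/139) = 0.72 points
- 95% limit = 1.96 × 0.72 = 1.41 points
- Slope on baseline at r = 0.4, s1 = 8: 0.4 × 8 / 6.04 = 0.53
- Shift in the change estimate at the 95% limit: (1 − 0.53) × 1.41 = 0.66 points
- Shift in an unadjusted 6-month comparison: 0.53 × 1.41 = 0.75 points
- Shift in the change estimate at one SE: (1 − 0.53) × 0.72 = 0.34 points

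The planned difference is 4 points, so 0.66 is about one-sixth of it. At s1 = 12 and r = 0.5 the slope is 0.99 and the shift in the change estimate is close to zero.

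**4. What it does to power for a 4-point difference (normal approximation).** The range runs from 281 analysed down to 211 after the assumed 25% attrition.

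- s1 = 8, r = 0.3 to 0.5: raw change has about 93% power or more throughout, and ANCOVA adds at most about 4 percentage points.
- s1 = 12, r = 0.3 to 0.5: ANCOVA adds 0 to 2 percentage points.

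**The case against.** The strongest reply is that the article is silent on adjustment and does not rule it out. Section 2.3.1 mainly defines outcomes, and Section 2.13 keeps "logistic or linear regression analysis, mixed models, and, if necessary, Cox regression analysis based on registry data will be utilized". Naming change as the outcome does not exclude adjustment either: with baseline in the model, regressing change or the 6-month score gives the same treatment estimate. A condensed article may leave the covariate set to a fuller document. This stands. A reader might infer that the plan has decided against adjustment, but the text does not support that.

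Three other inferences also fail.

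- **That the primary contrast is described in several conflicting ways.** The sentence about values at baseline and at 6 months belongs to the secondary outcomes. Section 2.5 itself starts from change in MADRS, and its later phrase about mean values serves mainly to set the continuous outcome apart from the responder outcome. The wording is loose, but it is not a set of rival primary analyses.
- **That a significance test between arms at baseline is planned.** The text says values are compared. It mentions no test or p-value.
- **That the primary contrast could easily be picked after seeing the results.** Section 2.7 keeps the allocation code sealed until the intervention analyses, Section 2.9 blinds the analysts during the RCT, and Section 3.8 promises open scripts. These do not fix a model, but they limit the risk.

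It is also fair to say that the gain may be small, as the rows for a 6-month SD of 12 show.

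What survives is that the article does state contrasts, that those contrasts carry no baseline covariate, and that a method at least as precise in large samples is available from data already collected.

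**Conclusion.** The point holds as a recommendation to specify a better method. It does not show an error in the trial. The stated contrasts are unbiased over repeated randomisation. The imbalance shift is conditional on the baseline difference that actually arose, which the article does not report by arm.

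The direction is secure: in large samples a baseline-adjusted contrast is never less precise than raw change or 6-month values alone. The size is not, because it rests on an assumed 6-month SD and correlation. ANCOVA variance is 0.81 to 0.92 of change-score variance at an SD of 8 and r from 0.3 to 0.5, and 0.60 to 1.00 over SD 6 to 12 and r from 0.2 to 0.5. The shift of about 0.7 points applies to a baseline difference at its 95% limit with r = 0.4 and SD 8. The baseline SD comes from all 319 subjects, and the imbalance limit uses all 281 randomised; a smaller analysis set would widen that limit.

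This is worth doing before the analysis, because the gain may be modest but the cost is wording.

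**What to change.** - **Primary.** State the primary estimate as the arm difference in 6-month MADRS, or equivalently in change, from one named model with baseline MADRS as covariate. ANCOVA, or the 6-month contrast of a repeated-measures model adjusted for baseline, would serve.
- **Continuous secondary outcomes and biomarkers.** Use the same form, each with its own baseline value as covariate. Use a log scale for skewed markers, with a rule for values reported as zero (Table 3 gives a minimum of 0.0 for high-sensitivity CRP).
- **Baseline values by arm.** Present them descriptively only, and reword the last sentence of the secondary outcomes accordingly.
- **Alignment.** Use one description of the primary contrast in Sections 2.3.1, 2.5 and 2.13. In Section 2.5, say whether the SD of 12 refers to the score or to the change.

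The cost is a few sentences in the protocol or analysis plan. No new data are needed, since baseline MADRS is complete.
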